## Abstract

Background

Self-medication (SM), a common practice globally, possesses a dual challenge of being a self-care strategy and a potential source of harm observed across all age groups. The study is being conducted to gauge the prevalence of SM of prescription drugs with their over-the-counter access, thus addressing the delicate balance between self-care and self-harm related to SM.

Material and methods

This ongoing convergent parallel mixed method study with quantitative and qualitative components will be conducted on a sample size of 180 subjects aged more than 18 years from an urban community. For the quantitative component, a semi-structured questionnaire will assess the prevalence of SM, types of medications used, reasons for self-medicating, and socio-demographic factors influencing these practices. Concurrently, qualitative interviews delve deeper into the beliefs shaping SM practices. Sampling will be purposive to capture diverse perspectives, with data analyzed using statistical tools.

Results

This study protocol will offer a comprehensive understanding of the prevalence and determinants of SM practices. The quantitative data provide numerical insights into SM trends, while the qualitative findings elucidate the nuanced factors driving individuals' SM choices.

Conclusions

A multifaceted view of SM practices will be provided, aiding in developing interventions to promote safe and effective self-care while mitigating the risks of self-harm through SM. Anticipated findings can include a widespread prevalence of SM amongst the general urban populace. Significant associations can also be expected to be found with various independent variables. The results will be instrumental in informing public health policies and healthcare practices toward enhancing patient safety and well-being.

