Research indicates that the decision to self-medicate is influenced by a multitude of personal, organizational, and environmental factors [12]. Self-care gained attention and notoriety during the COVID-19 pandemic when people started practicing hand hygiene, wearing masks, and performing self-testing at home [13]. SM is a practice observed across all age groups, but a particular focus is directed toward the elderly concerning treatment and medication issues. Numerous studies have highlighted the elderly as the predominant medicine consumers in many countries, a trend also observed in Iran. This heightened medication consumption among the elderly can be attributed to several factors, including the increased prevalence of various diseases associated with aging. Conditions, such as diabetes, cardiovascular disease, and cancer, are prevalent among a significant portion of the elderly population. Additionally, the presence of multiple chronic diseases concurrently, known as comorbidity, is widespread in this age group and often necessitates increased medication usage [7]. SM has long been a prevalent practice within the general populace. This phenomenon is driven by various factors, including the desire for self-care, empathy toward unwell family members, limited access to healthcare services, economic constraints, lack of awareness, misconceptions, widespread advertising, and the availability of medications outside of traditional medical outlets. Additionally, the literature suggests that reasons for engaging in SM include perceptions of illness severity, past experiences with similar illnesses, financial considerations, and difficulties accessing healthcare professionals [14,15]. SM practices should not be universally deemed harmful. OTC medications, available without a prescription, often offer convenience and cost savings for patients. Particularly in remote areas such as hill regions, tribal communities, and other underserved areas with limited access to healthcare professionals, SM remains a crucial recourse for addressing minor symptoms due to the scarcity of medical personnel [16]. Few studies have been conducted at a community level in India to evaluate the prevalence of SM practices. Such studies hold the potential to offer valuable insights into the motivations behind patient’s adoption of this practice. Moreover, they could aid policymakers and regulatory bodies in refining drug regulations, revising the list of essential medicines, and addressing safety concerns related to OTC medications. With this background, the study protocol aims to estimate the prevalence of SM of prescription drugs with their OTC access and the risk practice and identify potential factors that could influence SM practices in pharmacy outlets of Wardha along with reviewing policies pertaining to OTC and prescription drugs and identifying improvements to mitigate the risk practices.

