
## Materials and methods

Study design, participant, and setting

A convergent parallel mixed method study design with a quantitative component as a cross-sectional study and a qualitative component as an in-depth interview will be used for data collection for a period of 24 months from urban communities and pharmacies of Wardha. Before data collection, informed consent from study participants will be obtained, clearly outlining the purpose of the study, benefits and potential risks, voluntary participation, and the right to withdraw at any time. Ensuring participant confidentiality and privacy while collecting data is essential, and any ethical considerations or limitations in data collection will be carefully addressed to uphold research ethics standards. The study sought approval on 01.03.2024 from the Institutional Ethics Committee of Datta Meghe Institute of Higher Education and Research with reference number DMIHER(DU)/IEC/2024/126 to ensure the research adheres to the ethical guidelines, respects participant rights, and meets established ethical standards and has been registered for the Clinical Trials Registry - India with the registration number CTRI/2024/07/069886.

Inclusion and exclusion criteria

Subjects over 18 years and above who reside in Wardha and visited the pharmacy outlets to purchase medicine(s) during the study will be included in the study. Individuals participating willingly, voluntarily, and providing informed consent, who have a history of SM or are currently engaging in SM practices, and who have the cognitive ability to understand and respond to questions and participate in qualitative interviews. Doctors and healthcare workers who have knowledge of medications, individuals with cognitive impairments, and pregnant or breastfeeding women will be excluded from the study.

Sample size

The sample was calculated based on,

n = [Z2 P (1-P)]/d2

Z is the statistic corresponding to the level of confidence,

P is the expected prevalence,

d is precision (corresponding to effect size).

Sample size calculation

Assumptions:

Precision = 5.0% (0.05)

Prevalence = 11.9% (0.10) [16]

Z = 1.96

N = 1.96*1.96*0.119 (0.881)/0.0025

The final sample size based on the prevalence of 11.9% was 161. Assuming 10.0%-12.0% dropouts, the estimated sample taken was 180.

Data collection tools and methods

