**Figure 1 FIG1:**
[figure not shown]
Schematic flowchart for mixed method study design

**Table 1 TAB1:** Description of the tool included in this study

Section	Details
Part A	Sociodemographic characteristics
	Age
	Place of residence
	Religion
	Marital status
	Level of education
	Occupation
	Family type
	Socioeconomic status (evaluated using Modified B.G. Prasad Scale)
Part B	Self-medication behaviors in the past year
	Patterns of self-medication (e.g., frequency, duration)
	Types of medications used
	Reasons for self-medication (e.g., convenience, cost, perceived need)
Part C	Pharmacist's perspective on self-medication practices
	Inquiry by a doctor to pharmacist
	Pharmacist's observations
	Customer behavior related to self-medication

Data analysis

All collected data will be analyzed using Statistical Package for the Social Sciences (IBM SPSS Statistics for Windows, IBM Corp., Version 23, Armonk, NY). Quantitative data will be presented as mean ± standard deviation, while qualitative data will be expressed as frequencies and percentages. Descriptive statistics will summarize and present sociodemographic characteristics, SM frequencies, patterns, and types of medications used. Measures, such as mean, median, and standard deviation, will be utilized to describe central tendency and variability. Inferential statistics will be employed to analyze relationships and associations between variables. Correlation analysis may explore the degree of association between factors such as age, socioeconomic status, and SM frequency. Furthermore, the chi-square test will assess the impact of demographic variables on SM practices. Group comparisons will be conducted using the student t-test. A p-value <0.05 will be considered statistically significant.

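### The single eligibility list requires past or current self-medication and is not limited to the interviews; applied to the survey, it selects on the outcome and gives the prevalence the wrong denominator

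*Protocol article*

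**What the plan says.** All references are to the protocol article.

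- **Entry.** Inclusion and exclusion criteria (Materials and methods) is one section for the whole mixed-methods study. Its first sentence takes adult Wardha residents who "visited the pharmacy outlets to purchase medicine(s) during the study will be included in the study". Its second adds consent, cognitive ability and people "who have a history of SM or are currently engaging in SM practices". The exclusions follow: "Doctors and healthcare workers who have knowledge of medications, individuals with cognitive impairments, and pregnant or breastfeeding women will be excluded". None of them restricts the SM condition to one strand or readmits people who have never self-medicated.
- **Aim.** The Introduction closes by saying that "the study protocol aims to estimate the prevalence of SM of prescription drugs with their OTC access and the risk practice", and that influencing factors will be identified. The Abstract gives this task to the quantitative strand: "a semi-structured questionnaire will assess the prevalence of SM, types of medications used, reasons for self-medicating, and socio-demographic factors influencing these practices".
- **Target population.** The Abstract looks ahead to a result for a wide population: "Anticipated findings can include a widespread prevalence of SM amongst the general urban populace".
- **Size.** Sample size uses the single-proportion precision formula with P = 11.9%, d = 5 points and Z = 1.96. It gives 161, raised to 180 for dropout.
- **Analysis.** Data analysis states that "the chi-square test will assess the impact of demographic variables on SM practices". It also mentions correlation with SM frequency, and t-tests whose groups are not named.
- **Measurement.** Part B of the questionnaire (Table 1) covers SM behaviour over the past year.

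**The concern.** A prevalence needs a denominator that includes people with and without the behaviour. If a history of the behaviour is a condition of entry, those without it never reach the denominator, and no later analysis can put them back. The condition suits the in-depth interviews, which explore why people self-medicate. It does not suit a survey meant to say how common SM is and who does it. The Abstract describes the study as ongoing, so each month of recruitment under this rule may add subjects who cannot contribute to the prevalence estimate.

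**Working it through.** **Inputs.** P = 0.119, d = 0.05, Z = 1.96, n = 161 before dropout and 180 after (Sample size). The range 29.1% to 55% is the Indian prevalence cited in the Introduction.

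**1. The plan's own figure.** n = Z²P(1−P)/d² = 1.96² × 0.119 × 0.881 / 0.0025 = 161.1. The stated 161 reproduces. For dropout, 161/0.90 = 179, 161/0.88 = 183 and 161 × 1.12 = 180.3, so 180 is consistent with the stated 10% to 12%. The arithmetic is not the problem.

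**2. What that figure assumes about who is enrolled.**

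| n | Users, n × 0.119 | Non-users, n × 0.881 |
|---|---|---|
| 161 | 19.2 | 141.8 |
| 180 | 21.4 | 158.6 |

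The calculation therefore expects roughly seven in eight subjects to be non-users.

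**3. What the entry rule gives if applied to the survey.** All 180 subjects have self-medicated at some time and none has not. Ever-SM is 180/180 = 100%, with an exact 95% lower limit of 0.025^(1/180) = 98.0%. This reflects the entry rule and says nothing about Wardha.

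**4. Narrower outcomes.** Let q be the proportion of the unselected population who have ever self-medicated, and p the proportion with the narrower outcome (past-year SM, or SM of prescription drugs). Among ever-users the survey estimates p/q, not p. The article does not give q. As an illustration only, assume that p is the planning value of 11.9% and that q lies at either end of the cited range:

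- q = 0.55: 0.119/0.55 = 21.6%
- q = 0.291: 0.119/0.291 = 40.9%

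The result is below 100%, but on these assumptions it is about 1.8 to 3.4 times the quantity sought (1/0.55 and 1/0.291). The data cannot correct it, because q is not observed.

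**5. With the condition removed from the survey.** At n = 180 and P = 0.119, the half-width is 1.96 × √(0.119 × 0.881/180) = 4.7 points, within the planned 5. About 21 users can be compared with about 159 non-users.

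**The case against.** The strongest reply is that the SM condition was never meant for the survey. The first inclusion sentence is complete and carries no such condition. The second is a fragment without a main verb, and its last item is taking part in the qualitative interviews. Data collection tools and methods names the general population as a source, and a planning value of 11.9% shows that non-users were expected. This may well be what was intended. But the same fragment carries consent and cognitive ability, which apply to everyone, and no sentence divides eligibility by strand. The Figure 1 flowchart could not be read here and should be checked for such a split. If that was the intention, the text still has to say so, because recruiters following it would turn non-users away.

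Two stronger readings are tempting, and the article supports neither.

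- **A reader might infer that the study's prevalence is fixed at 100% whatever is measured.** That is exact only for ever having self-medicated. Part B covers the past year and the Introduction's aim concerns prescription drugs. Someone who once took a non-prescription remedy could enter and be a case of neither.
- **A reader might infer that the planned tests cannot be computed.** Data analysis names no user versus non-user test. Frequency, duration, drug type and reasons vary among users, so the correlations and chi-square tests can be run on them. What is lost is any assessment of who self-medicates and who does not.

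The Limitations section raises possible unrepresentativeness of Wardha adults in general terms. It does not disclose selection on the outcome.

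**Conclusion.** The point holds as a contradiction in the text: the entry rule as written conflicts with the prevalence aim and with the basis of the sample size. Followed literally, it removes every never-user from a survey sized on about 142 non-users in 161. Ever-SM becomes 100% by design, the narrower SM measures become proportions among self-medicators, and factors associated with being a self-medicator cannot be assessed. Analyses of patterns among users are unaffected.

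This rests on the SM condition applying to the survey. The wording allows that reading and nothing in the text rules it out, although the authors may have intended otherwise. The conclusion does not depend on the illustrative values of q. It should be settled before recruitment goes further, because the analysis cannot recover people who were never enrolled.

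**What to change.** Divide the eligibility section by strand.

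- **Survey:** enrol otherwise eligible adults whatever their SM history. Define the outcome as any SM in the past 12 months, to match Part B, and report SM of prescription drugs separately, to match the aim.
- **In-depth interviews:** keep the condition of past or current SM for the customers selected.

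If the survey is to stay restricted to self-medicators, restate the aim as patterns of SM among self-medicators, drop the prevalence claim, and replace the sample-size basis.

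**Cost.** A short eligibility amendment and notification of the ethics committee. The planned 180 need not rise, since the half-width is 4.7 points at P = 11.9%. Subjects already enrolled under the SM condition should be left out of the prevalence estimate and may need replacing; the article does not say how many there are.

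The amendment does not by itself deliver a community prevalence. Purposive sampling and recruitment at pharmacies still limit the estimate to medicine buyers, which is a separate point.

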**Figure 1 FIG1:**
[figure not shown]
Schematic flowchart for mixed method study design

**Table 1 TAB1:** Description of the tool included in this study

Section	Details
Part A	Sociodemographic characteristics
	Age
	Place of residence
	Religion
	Marital status
	Level of education
	Occupation
	Family type
	Socioeconomic status (evaluated using Modified B.G. Prasad Scale)
Part B	Self-medication behaviors in the past year
	Patterns of self-medication (e.g., frequency, duration)
	Types of medications used
	Reasons for self-medication (e.g., convenience, cost, perceived need)
Part C	Pharmacist's perspective on self-medication practices
	Inquiry by a doctor to pharmacist
	Pharmacist's observations
	Customer behavior related to self-medication

Data analysis

All collected data will be analyzed using Statistical Package for the Social Sciences (IBM SPSS Statistics for Windows, IBM Corp., Version 23, Armonk, NY). Quantitative data will be presented as mean ± standard deviation, while qualitative data will be expressed as frequencies and percentages. Descriptive statistics will summarize and present sociodemographic characteristics, SM frequencies, patterns, and types of medications used. Measures, such as mean, median, and standard deviation, will be utilized to describe central tendency and variability. Inferential statistics will be employed to analyze relationships and associations between variables. Correlation analysis may explore the degree of association between factors such as age, socioeconomic status, and SM frequency. Furthermore, the chi-square test will assess the impact of demographic variables on SM practices. Group comparisons will be conducted using the student t-test. A p-value <0.05 will be considered statistically significant.

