## Introduction

Self-medication (SM) is described as the acquisition and ingestion of one or more drugs without consulting a medically qualified physician for diagnosis, treatment, or prescription oversight. It encompasses the use of non-prescription medications by individuals without professional guidance. The wide accessibility of diverse drugs and insufficient and unequal healthcare services contribute to a rise in SM practices in developing nations such as India [1]. Studies carried out in India have observed SM prevalence rates ranging from 29.1% to 55%, varying based on study methodologies and geographical locations [2,3]. Previous studies conducted both domestically and Internationally have identified numerous factors, ranging from geographic isolation to sociodemographic variables, as potential determinants contributing to the widespread practice of SM. However, prior research within this country has not thoroughly examined SM through a socio-psychological lens, which could encompass societal perceptions regarding medication, access to healthcare services, and subsequent care-seeking behaviors among individuals who engage in SM [4].

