## Discussion

Many factors can lead people to take their own medication, including the need for self-care, empathy for sick family members, a lack of health services, poverty, misinformation, misbelief, and the accessibility of medications in places other than pharmacies. Research conducted in two phases in India has indicated the prevalence of SM among students to be 74.6% and 69.4% [17]. Similar studies suggest that literacy level, history of SM, profession, unavailability of medical insurance, lack of priority in consulting medical professionals, low economic status, the female sex, and staying in an urban setting were among the factors associated with SM practices [17]. Given the growing public health concerns around SM with prescription drugs and OTC access, this study focuses on risk practice prevalence, its use, its safety, and reasons for using it. On one side, the availability of medicines on an OTC basis improves access to healthcare for people living in settings lacking in resources or in places in need of adequate healthcare infrastructure. On the other, it increases the probability of severely harming one's health by the misuse of medications [7]. The dichotomy needs thorough investigation, allowing us to balance accessibility and responsible drug consumption. It is essential for individuals using medications to have appropriate medical comprehension regarding dosage, timing of administration, and potential ramifications of overuse, as inadequate information could lead to major repercussions, including antibiotic resistance, skin issues, hypersensitivity, allergies, and dependency. As it stands, regulations around the OTC availability of certain prescription drugs vary globally across jurisdictions. There is an urgent need to enhance awareness and enact regulations aimed at promoting prudent and safe practices regarding SM. There is a potential to encourage its rational use and mitigate the emergence of microbial resistance by fostering and improving its knowledge. Despite existing research on this subject, SM has slipped under the radar regarding receiving the attention it warrants as a research area. Moreover, most studies on this topic have been conducted in countries with vastly different healthcare systems and cultural contexts from that of India, rendering their findings potentially non-transferable. It is imperative to gather data on the prevalence of SM in India as well as explore their related factors to facilitate the enhancement of SM practices within the country.

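### The aim is prevalence of self-medication with prescription drugs and of risk practice, but the definition, questionnaire outcome and planned summaries concern self-medication with any drug, and risk practice is undefined

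*Protocol article*

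**What the plan says.** **Aim.** The Abstract says the study is meant to "gauge the prevalence of SM of prescription drugs with their over-the-counter access". The Introduction closes with the aim to "estimate the prevalence of SM of prescription drugs with their OTC access and the risk practice". The Discussion widens this: "this study focuses on risk practice prevalence, its use, its safety, and reasons for using it".

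**Definition.** The Introduction describes SM as "the acquisition and ingestion of one or more drugs without consulting a medically qualified physician for diagnosis, treatment, or prescription oversight". The next sentence reads "It encompasses the use of non-prescription medications by individuals without professional guidance".

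**Tool.** In the Abstract's methods, "a semi-structured questionnaire will assess the prevalence of SM, types of medications used, reasons for self-medicating, and socio-demographic factors influencing these practices". Table 1, Part B covers behaviour over the past year under three entries: patterns (with frequency and duration as examples), "Types of medications used", and reasons. Part C covers the pharmacist's perspective.

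**Other sources.** Data collection tools and methods says that OTC lists, regulations, prescription records, medication bags and home medicine inventories will also be used.

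**Analysis.** Data analysis promises descriptive summaries of SM frequencies, patterns and medication types, and tests of association with SM. It names no outcome restricted to prescription drugs, and none for risk practice or safety.

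**The concern.** The article treats OTC self-medication as a legitimate part of self-care and unsupervised use of prescription drugs as the potential harm. The Discussion presents the tension between the two as what needs investigating. A prevalence that counts both in one numerator loses that contrast.

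Under the printed definition, someone who took only a legal OTC product is a self-medicator. If the any-SM percentage is then read against the stated aim, that person counts as a case of prescription-drug SM. The associations with age, education or socioeconomic status would have the same ambiguity, because the factors behind buying an OTC product need not be those behind obtaining a prescription-only drug without a prescription.

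Risk practice is the weaker-supported half of the aim. It is to be estimated as a prevalence, yet no statement says what counts as a risk practice, and no risk or safety outcome appears in the described tool or analysis. The Abstract calls the study ongoing, so prescription status and harms that are not asked about at interview would be hard to recover later.

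**Working it through.** **1. The passages side by side**

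| Element | Where | Drugs covered | Risk practice or safety |
|---|---|---|---|
| Aim | Abstract; end of Introduction | Prescription drugs with OTC access | Risk practice named in the Introduction |
| Focus | Discussion | Prescription drugs and OTC access | Risk-practice prevalence and safety named |
| Definition, first sentence | Introduction | Any drug taken without consulting a physician | None |
| Definition, second sentence | Introduction | Names non-prescription drugs | None |
| Questionnaire outcome | Abstract, methods | SM in general | None |
| Tool | Table 1, Part B | Types of drug, legal status not mentioned | None beyond frequency and duration |
| Summaries | Data analysis | SM in general | None |

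The aim is narrower than every element that would deliver it. Risk practice and safety appear among the aims and focus and then drop out.

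**2. What classifying a case would need**

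To count a participant as a case of prescription-drug SM, two facts are needed for each product: (a) whether it is prescription-only, and (b) whether it was obtained without a current prescription. Fact (a) could be derived from the medication type, if recorded closely enough, together with the OTC lists and regulations. Fact (b) could in part come from prescription records. The article does not say that these sources serve this purpose or that they are collected for all 180 participants. They are introduced in the paragraph that describes the interviews.

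**3. The plan's own figure**

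Inputs from Sample size calculation: Z = 1.96, P = 0.119, d = 0.05.

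n = Z² P(1 − P)/d² = 1.96² × 0.119 × 0.881/0.0025 = 161.1, which reproduces the stated 161.

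For dropout, 161/0.90 = 178.9 and 161/0.88 = 183.0, so 180 lies within the range. The arithmetic does not settle the present point: P is called only the expected prevalence, without saying whether it refers to any SM or to prescription-drug SM.

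**4. Size of the mixing**

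Let A be the prevalence of any SM and s the share of self-medicators who used only OTC products. Prescription-drug SM is then A(1 − s), and reading A in its place overstates it by

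A / [A(1 − s)] = 1/(1 − s).

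The documents give no value of s. As pure illustration, s = 0.30 gives 1/0.70 = 1.43, s = 0.50 gives 1/0.50 = 2.0, and s = 0.70 gives 1/0.30 = 3.33. These values of s are assumptions with no anchor in the article.

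**The case against.** The strongest defence is that this is a condensed article. Table 1 describes the tool by section, and some entries give only examples. Item wording belongs in the full questionnaire, which is not shown. The definition stands in the Introduction as background, and a broad concept can coexist with a narrower aim. Nothing printed says that an OTC-only buyer will be counted as a prescription-drug case. Part C and the long open interviews will also yield material relevant to risk.

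Much of this stands, and it rules out four stronger readings that a reader might infer:

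- *The headline outcome cannot be computed.* Not supported. Medication types together with the OTC lists, regulations and prescription records could classify each drug.
- *The questionnaire has no item on prescription status or harm.* Not shown. A section-level table that omits an item does not prove that the instrument lacks it.
- *The definition excludes prescription drugs.* It does not. Its first sentence covers any drug taken without consulting a physician. The definition is too broad for the aim, and its second sentence sits awkwardly with the first.
- *The prevalence is overstated 1.4 to 3.3 times.* This depends on an assumed share of OTC-only users, and on the any-SM figure being presented as prescription-drug SM.

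The defence does not remove the mismatch between aim, questionnaire outcome and planned summaries, all of which are printed. Nor does it supply a meaning for risk practice: frequency, duration and pharmacists' observations do not become a prevalence without a rule for what counts.

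**Conclusion.** The concern holds as an inconsistency in the outcome. The aim is prevalence of prescription-drug SM and of risk practice, with safety as a further focus, while the definition, questionnaire outcome and planned summaries refer to SM with any drug. No rule separating prescription-only from OTC products is stated, although the sources to apply one are already planned. Risk practice is undefined, and no risk-practice or safety outcome appears in the described tool or analysis; this is the firmer half of the point.

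Followed as printed, the study would report any-SM prevalence under a prescription-drug aim. The direction is clear if that figure is read against the aim: it overstates prescription-drug SM whenever some self-medicators used only OTC products. The amount cannot be determined from the documents. The conclusion rests on the printed aim, definition, outcome and analysis, and not on assumptions about the unseen questionnaire.

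**What to change.** 1. Define the primary outcome as use, in the past year, of at least one prescription-only drug obtained without a current prescription. The past-year window matches Part B.
2. For every participant, record each product's name and whether a prescription existed. Code drug status from the OTC lists and regulations named under Data collection tools and methods.
3. Report any SM and OTC-only SM separately from the primary outcome. Other arrangements of these outcomes would also work, provided the one that matches the aim is identifiable.
4. Define risk practice in advance and support it with a few yes/no items, including suspected adverse effects, and add the matching summary to Data analysis. Otherwise drop risk-practice prevalence and safety from the aims.
5. If the full questionnaire already holds such items, say so and state the coding rule.

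The cost is a slightly longer questionnaire and a coding step against lists already being gathered.

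This does not address a separate problem: Inclusion and exclusion criteria requires a history of SM or current SM, which bears on whether any population prevalence can be estimated and needs its own correction.
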